#### Personalised hip therapy

PHT is a package of physiotherapist-led best conservative care for FAI. It was developed during the feasibility study and ‘road-tested’ during the pilot trial (HTA 10/41/02).^14^ The care being offered represents a consensus of what physiotherapists, physicians and surgeons regard as ‘best conservative care’ for FAI. PHT will be delivered by a senior physiotherapist at each site, who will be trained at a FASHIoN PHT workshop, and supported in PHT delivery by a physiotherapy research facilitator.

PHT consists of four key components:
An assessment of pain, function and range of hip motion,Patient education and advice,Help with pain relief (which may include up to one radiographic-guided intra-articular steroid injection where pain prevents performance of the exercise programme),An exercise programme that has the key features of individualisation, progression and supervision.

The intervention is delivered over a minimum of six patient contacts (at least three of which must be face-to-face treatment contacts, others can be by telephone and email) over a period of 6 months. In situations where the patient needs additional review, support or guidance, further sessions with the physiotherapist are permitted up to a maximum of 10 contacts. Evidence of exercise individualisation, supervision and progression will be sought from individual participant physiotherapy case report forms (CRFs). Accuracy of CRFs will be audited against the physiotherapist's treatment notes.

The PHT CRFs will be assessed for intervention fidelity to identify participants for a secondary analysis by the panel that developed the protocol for PHT, including: [name] (Senior Academic Research Physiotherapist), [name] and [name] (UK; Extended Scope Musculoskeletal Physiotherapists) and PW (Academic Orthopaedic Surgeon).

Crossover of participants between interventions can be problematic in trials of this nature. In order to minimise, this care will be taken prior to enrolment in the trial to ensure potential participants:
Are willing to receive either intervention,Understand both treatments are thought to provide benefit,Are willing to remain with their allocation for 12 months,Understand that both interventions may take 6 months to improve symptoms.^12^
^19^

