In instances where patients are not satisfied with how their treatment is progressing prior to reaching the primary outcome, they will be able to have a further consultation with their treating surgeon where they would be treated in their best interests.

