### Sample size calculation

The development work for iHOT-33 reported a mean iHOT-33 score of 66 and an SD of 19.3 in a heterogeneous population with a variety of hip pathologies. The baseline iHOT-33 data from our pilot trial (HTA grant 10/41/02) suggests the target population of patients being considered for hip arthroscopy for FAI have lower scores with less variability, with a mean of 33 and SD of 16. The MCID for iHOT-33 in this population is 6.1 points.^21^

Our sample size calculation is therefore based on an SD of 16 and a between-group MCID of 6.1: a standardised effect difference between groups at 12 months of 0.38. The expected sample size for 90% power to detect an effect size of 0.38 at 12 months, at a 5% significance level, assuming an approximately normal distribution of the iHOT-33 score is 292. Allowing for 15% loss to follow-up at 12 months, we will recruit a sample of 344 participants over 26months in the UK (172 in each group).

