### Statistical analysis

The primary analysis will be of differences in hip-related quality of life (iHOT-33) at 12 months between the two treatment groups, blinded, on an intention-to-treat basis and presented as the mean difference between the trial groups with a 95% CI. iHOT-33 data will be assumed to be normally distributed; possibly after appropriate variance-stabilising transformation.

The minimisation randomisation procedure should ensure treatment group balance across recruiting sites. We have no reason to expect that clustering effects will be important for this study, but the possibility of such effects will be explored as part of the analysis.^33^ We plan to account for clustering by generalising a conventional linear (fixed-effects) regression approach to a mixed-effects modelling approach; where patients are naturally grouped by recruiting sites (random-effects) and, if amenable to analysis, also by physiotherapist and surgeon. This model will formally incorporate terms that allow for possible heterogeneity in responses for patients due to the recruiting centre, in addition to the fixed effects of the treatment groups, and patient characteristics that may prove to be important moderators of treatment effect such as age, gender and FAI type. This analysis will be conducted using specialist mixed-effects modelling functions available in the software packages Stata (StataCorp. 2015. Stata Statistical Software: Release 14. College Station, Texas, USA: StataCorp LP) and R (http://www.r-project.org/). All tests will be two-sided and considered to provide evidence for a statistically significant difference if p values are <0.05 (5% significance level).

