Secondary analyses will be performed using the above strategy for other approximately normally distributed outcome measures, including iHOT-33 at 6 months, SF-12 (and computed subscales) and EQ5D. Differences in dichotomous outcome variables such as AEs, complications related to the trial interventions and the need for further procedures will compared between groups using χ^2^ tests (or Fisher's exact test) and mixed-effects logistic regression analysis will be undertaken, adjusting for the stratifying variables, with differences between trial intervention groups quantified as ORs (and 95% CIs). The temporal patterns of any AEs will be presented graphically and if appropriate, a time-to-event analysis (Kaplan-Meier survival analysis) will be used to assess the overall risk and risk within individual classes of AEs. Ordinal scores for patient satisfaction will be compared between intervention groups using proportional odds logistic regression analysis, assuming that the estimated intervention effect between any pair of categories is equivalent.

Our inferences will be drawn from the intention-to-treat analysis. We will perform two exploratory secondary analyses. One will compare patients who received surgery and those who received conservative care. A second exploratory analysis will compare patients randomised to surgery or PHT and received treatment deemed to be of a high fidelity by the respective review panels. We plan to perform a subgroup analysis by FAI type because it is possible that treatment effect is moderated by type. We anticipate that adequate steps have been taken to prevent crossovers from being a major issue for this study. Therefore, we expect the main intention-to-treat analysis to provide definitive results. An independent Data Monitoring Committee (DMC) will monitor crossovers and adherence to treatment and advise on appropriate modifications to the statistical analysis plan as the full trial progresses.

The initial feasibility and pilot studies (HTA 10/41/02) were designed explicitly to assess feasibility and measure recruitment rates, and not to estimate treatment effectiveness. Data from the pilot will be pooled with data from the full trial, and analysed together.

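### The two exploratory non-ITT comparisons use groups formed after randomisation, and the as-treated one can lie further from the effect of receiving surgery than the ITT estimate does

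*Protocol article*

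**What the plan says.** Under Statistical analysis, the protocol article says inferences will come from the ITT analysis and then names two exploratory secondary analyses. The first groups patients by treatment received: "One will compare patients who received surgery and those who received conservative care". The second is a selected subset: "A second exploratory analysis will compare patients randomised to surgery or PHT and received treatment deemed to be of a high fidelity", as judged by a review panel for each arm.

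Three other places bear on how these groups form.

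- The Personalised hip therapy subsection provides that, if patients are unhappy with progress before the primary outcome, "they will be able to have a further consultation with their treating surgeon where they would be treated in their best interests".
- The Arthroscopic surgery subsection has an international panel judge adequacy from operation notes, intraoperative images and postoperative MRI. PHT fidelity is judged from case report forms "by the panel that developed the protocol for PHT". PHT is defined as at least six contacts over 6 months.
- Statistical analysis expects crossover not to be a major issue. It asks the Data Monitoring Committee (DMC) to monitor crossovers and adherence and to advise on changes to the analysis plan.

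No expected crossover rate is given.

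**The concern.** Neither comparison keeps the randomised groups. The protocol itself supplies an outcome-related route from PHT to surgery: dissatisfaction with progress. Early poor response plausibly predicts a low iHOT-33 at 12 months. An as-treated analysis takes such patients out of the conservative group and puts them into the surgery group. That raises the first mean, lowers the second, and pulls the contrast down for reasons unrelated to what surgery does.

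The high-fidelity subset is filtered differently in each arm. On the PHT side, reaching the required contacts plausibly depends on how the patient is doing. On the surgical side, selection is mainly on technical adequacy, and so on case difficulty and surgeon. The two retained groups need not be comparable.

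What is at stake is the secondary question of what surgery does for those who receive it. These are the only two analyses the article names for treatment as actually received, and the first matters most if crossover occurs.

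**Working it through.** **1. The plan's own figure.** Inputs from Sample size calculation and Statistical analysis: difference 6.1, SD 16, two-sided 5%, 90% power, 15% loss. With the rounded effect size, n per arm = 2(1.960 + 1.282)²/0.38² = 145.5, so 146 per arm and 292 in total. Then 292/0.85 = 343.5, so 344. With the unrounded 6.1/16 the result is 145 per arm, 290 in total. The sample size reproduces and is not in dispute; 6.1, 16 and 146 are carried forward.

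**2. One-way switching (PHT to surgery), the route the protocol describes.** Let c be the share of the PHT arm that switches, g the prognosis of switchers minus stayers in points, and τ the true effect. Both c and g are assumptions.

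- ITT = τ(1 − c)
- As-treated = τ + 2gc/(1 + c)
- Complier-average = ITT/(1 − c) = τ, provided allocation acts only through receipt of surgery

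With τ = 6.1:

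| c | ITT | As-treated, g = −8 | As-treated, g = −16 |
|---|---|---|---|
| 5% | 5.79 | 5.34 | 4.58 |
| 10% | 5.49 | 4.65 | 3.19 |
| 20% | 4.88 | 3.43 | 0.77 |

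As-treated is further from 6.1 than ITT when 2|g|c/(1 + c) > cτ, that is |g| > τ(1 + c)/2. At c = 10% this is 6.1 × 1.1/2 = 3.4 points, about 0.2 SD. Below that gap, as-treated is the closer of the two, and with no gap it is unbiased.

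**3. The same with stated correlations.** Assume a prognostic factor correlated 0.7 with outcome and 0.5 with the tendency to switch. For c = 10% the mean of the switching tendency among switchers is 1.755 SD. Their prognosis is therefore lower by s = 16 × 0.7 × 0.5 × 1.755 = 9.83 points, and g = −9.83/0.9 = −10.92.

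- One way: bias = 2 × (−10.92) × 0.1/1.1 = −1.99. As-treated 4.1, ITT 5.5, complier-average 6.1.
- 10% each way, with good-prognosis patients moving from surgery to PHT: bias = −4cs = −4 × 0.1 × 9.83 = −3.93. As-treated 2.2, ITT 6.1 × 0.8 = 4.9, complier-average 6.1.

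A simulation with 146 per arm gave the same means: 4.11, 5.49 and 6.12 one way; 2.16, 4.86 and 6.10 each way.

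**4. Sensitivity to the prognosis–outcome correlation (10% each way).** At 0.5, s = 7.02 and as-treated is 6.1 − 2.81 = 3.3. At 1.0, s = 14.04 and as-treated is 6.1 − 5.62 = 0.5. This input drives the result.

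**5. Precision.** SE of ITT = 16 × √(2/146) = 1.87. The complier-average SE is about 1.87/0.9 = 2.1 one way and 1.87/0.8 = 2.3 each way (2.1 and 2.4 in the simulation).

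**6. High-fidelity subset.** If a share f of one arm is rated high fidelity and differs in prognosis by g from the rest of that arm, the contrast shifts by g(1 − f). For f from 90% to 60% and g from 8 to 16 points, the shift is 0.8 to 6.4 points. These inputs are also assumed, and selection in the same direction in both arms would partly cancel.

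**The case against.** The protocol already limits these analyses: it calls both exploratory and draws its inferences from ITT. It lists pre-enrolment steps against crossover, including willingness to stay with the allocation for 12 months, expects crossover to be minor, and gives the DMC a route to advise changes. The analysis plan is not shown and may add adjustment or a complier-average estimate. All of this stands, and it keeps the point away from the primary conclusion. It does not remove the selection, because the article itself fixes how the two sets of groups are formed.

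The two-way scenario is less well grounded than the one-way scenario. The article describes dissatisfied patients returning to the surgeon. It does not say that patients who improve while waiting forgo surgery, and such patients would not automatically count as having received conservative care.

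The alternative has its own weakness. The complier-average estimate returns 6.1 above because the model assumes allocation acts only through receipt of surgery. Here patients are unblinded, the outcome is self-reported, and the article says either intervention may take 6 months to improve symptoms. A patient who crosses over late counts as operated on by 12 months, has also had PHT, and may show little benefit yet. That objection stands and must accompany the estimate.

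A reader might also infer that the fidelity panels will see outcomes before rating. The article does not say so; this is unstated detail, not an error. Using different evidence to judge an operation and an exercise programme is unavoidable.

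**Conclusion.** The point holds as a limited one about two exploratory analyses. Both compare groups formed after randomisation, and the protocol's own provision for dissatisfied patients makes selection by prognosis plausible in the as-treated contrast. Under the assumptions in the working, 10% one-way switching puts as-treated 2.0 points below a true 6.1, against 0.6 for ITT. With 10% each way the shortfalls are 3.9 and 1.2. Switching rates and correlations are assumptions, so the actual size cannot be determined from the article.

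Two stronger readings are not supported. One is that the trial's main conclusion is compromised; it is not, since inference rests on ITT. The other is that the as-treated result would be expected to reverse sign. With 15% each way and the same correlations, s = 16 × 0.7 × 0.5 × 1.554 = 8.70 and the mean is still positive: 6.1 − 4 × 0.15 × 8.70 = 0.9. A negative mean (about −1.4) appeared at 15% each way only when the prognosis–outcome correlation was raised to 1.0.

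**What to change.** Make a complier-average causal effect the main exploratory estimate of the effect of treatment received. Use randomised arm as the instrument for receipt of surgery by 12 months, fitted by two-stage least squares with the primary model's covariates. State the exclusion restriction beside the result, and say why unblinded self-report and late crossovers make it questionable. If the as-treated and high-fidelity comparisons are kept, label them non-randomised and report them descriptively.

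The cost is analysis-plan wording and one extra model, with no change to conduct or sample size. The price is a wider interval (SE about 2.1 to 2.4 against 1.9 in the scenarios above) and reliance on an assumption that the data cannot test.

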### Economic analysis

An economic evaluation will be integrated into the trial design and will be conducted from the recommended NHS and personal social services perspective.^30^ Cost-effectiveness will be calculated using both within trial and lifetime horizons. Data will be collected on the health and social service resources used in the treatment of each trial participant until 12 months.

An incremental cost-effectiveness analysis, expressed in terms of incremental cost per quality-adjusted life year gained, will be performed. Results will be presented using incremental cost-effectiveness ratios and cost-effectiveness acceptability curves generated via non-parametric bootstrapping.

### Qualitative interview analysis

Participant interview transcripts will be analysed thematically, using methods of constant comparison derived from grounded theory.^31^ Emerging themes will be explored, looking for shared or disparate views among patients about their experiences, and among clinicians about their experiences of delivering the trial interventions. Focused conversation analysis will be undertaken on sections of recruitment appointments, and compared with the six-step good recruitment model developed in the pilot study to identify aspects of RCT presentation that are unclear, disrupted or hinder recruitment.^15^
^20^
^32^

### Data management

All of the data collected in this trial will be entered into a secure trial database held at WCTU. All data collected will be anonymised after the collection of baseline demographic data, and all participants given a unique trial number. Identifiable participant data will be held in a locked filing cabinet and coded with a trial participant number to tag identifiable data to the outcome data. The WCTU quality assurance manager will undertake audits of trial records in accordance with WCTU SOPs.

A DMC will be established comprised of members who are independent of the sponsor and who do not have competing interests. The DMC will review trial progress, interim data and safety aspects of the trial. They will also review the statistical analysis plan. Any recommendations will be fed back to the trial steering committee (TSC) by the DMC chair. Outcomes will not be analysed until all primary outcome data are collected. The trial may be stopped prematurely if mandated by the research ethics committee, the DMC or if funding ceases.

## Discussion

This protocol paper describes the FASHIoN trial; a multicentre RCT comparing hip arthroscopy to best conservative care (PHT) in order to establish the most clinically and cost-effective treatment for patients with FAI syndrome. Further details of the trial protocol can be found on the ISRCTN registry (ISRCTN64081839). This protocol will also be used for a randomised trial in Australia (ACTRN12615001177549). The results of the trial will be disseminated at international meetings and in peer-reviewed journals; to participants via post and to the public via the trial website.

The main strengths of this trial are that it is multicentre, pragmatic and randomised, making results generalisable across the NHS. Further strengths include a large sample size and the robust procedures to assess treatment fidelity.
